#### Unmet needs of the patient

A study-specific question is included at T1 to T4 to identify whether there were important needs that remained unaddressed during the rehabilitation care, and if so, which healthcare professionals the patient wished to be involved. It comprises of a yes-no question to ask whether there were needs not addressed during the last 3 months. If yes, patients can appoint the healthcare provider involved in the need. At the end of the program, the distress thermometer and problem list (completion at start and end of treatment) will be discussed with the patient. In addition, during the multidisciplinary team meeting problems are identified which were not properly addressed at the various time points [32–34].

#### Patient satisfaction

Level of satisfaction concerning the IHNR or USC will be assessed using a five-point scale, with 0 indicating very unsatisfied and 5 is very satisfied.

#### Clinical outcomes

Clinical outcomes include adverse events (e.g. pneumonia) during and after treatment, hospital admissions and medication use. These data will be obtained from medical records and a study-specific concise version of the Medical Consumption Questionnaire (MCQ) [26].

### Patient, tumor and treatment characteristics

Sociodemographic data (age, sex, marital status, educational background and employment status) of patients are gathered at baseline. Date of start of medical treatment is used to determine FU time points. Additional clinical data comprising treatment details of CRT and BRT (e.g. dose of systemic treatment, number of systemic cycles intended and provided) and tumor characteristics will be obtained from the medical record system. Information on progression of disease and recurrences will be evaluated throughout the study.

### Power calculation

To estimate the sample size required for this study, we used a one sample t-test power calculation. The power calculation was based on a comparison between the intervention and control group at end of follow-up, using a power (β) of 0.8 and a significance level of 0.05. We will recruit until we have included 128 patients in total for this analysis (64 are needed per arm) to be able to detect the expected effect-size (Cohen’s d) of 0.5 [35]. In our study we will use a repeated-measures design to allow for a more definitive evaluation of within-subject changes in the HRQOL summary score over time. Although, repeated measures can increase statistical power, we opted for a more conservative approach to sample size calculation by assuming a cross-sectional design. This should cover potential design effects such as attrition, or differences in baseline characteristics. Recruitment time is estimated at 2 years.

### Statistical analysis

Scores on the HRQoL questionnaires and the USER-P will be calculated according to published scoring algorithms [22, 24, 31].

We will look at group differences in HRQOL using a mixed effect growth model with random intercept and slope, nested within site (clusters of different hospitals). This approach takes into account the within and between person variability, and deals adequately with missing data [36]. If baseline differences are identified, these variables will be accounted for in the model. In case of non-ignorable dropout, which will be evaluated halfway during the study, we will correct the model for different patterns of missing values [37]. All analyses will be performed on an ‘intention to treat’ basis and will be adjusted for case mix by means of a propensity score analysis. Additional explorative analyses will be done on a ‘per protocol’ basis.

A generalized mixed-effects model using a logistic link function will be used to estimate the effects of IHNR on the proportion of patients at work, compared to USC, at each time point [38]. In this analysis, only patients are included who either are an employee, are self-employed, or do voluntary work at the baseline measurement.

Employment status, unmet needs and satisfaction of the patient will be analysed using descriptive statistics. Group differences in evaluation of satisfaction will be tested by means of the Chi-square test for trend. The unmet needs and the satisfaction of the patient will be evaluated cross-sectional, at each time point and at T4 respectively.

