## Methods

### Study design

We will perform a prospective controlled observational study comparing the effectiveness and cost-effectiveness of IHNR to USC for advanced HNC patients using Patient Reported Outcome Measures (PROMs). Primary objective is HRQoL. Secondary outcomes are functional HRQoL, return to work, societal participation, cost-effectiveness, unmet needs, clinical outcomes and patient satisfaction. Before the start of the treatment, patients in the intervention group are offered to participate in the IHNR. The intervention group consists of all eligible consenting patients treated in the NKI, despite participating or not in the program. The control group consists of advanced HNC patients treated in six Dutch HNC centers which are representative for the USC in the Netherlands; three academic and three community centers, providing mono- or multidisciplinary care.

This study does not fall under the Medical Research Involving Human Subjects Act (*Wet Medisch Wetenschappelijk Onderzoek*) due to the non-invasive nature of the study, but is submitted to and approved by the Dutch Medical Ethical Committees (registered: P16HNR). The study started in February 2017.

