## Discussion

To our knowledge, this is the first prospective multicenter study to evaluate the added value of the integrated character of a HNC interdisciplinary rehabilitation program. The study takes into account important outcomes of rehabilitation, including RTW and societal participation, which have not been sufficiently studied to date. As IHNR is an integrated program which is tailored to patients’ needs by individual and comprehensive assessment, we assume unmet needs are better addressed within this program.

The primary outcome expressed by the EORTC QLQ-C30 summary score, derived from the EORTC QLQ-C30 measurement instrument, offers a more reliable endpoint than the two-item overall QLQ-C30 score, often used in studies [20]. This study will take into account the variations in the provision of rehabilitation care between centers in the control group, due to the multicenter nature of this study including both academic and non-academic hospitals throughout the Netherlands. In addition, the cost-effectiveness analysis included in the study may provide valuable information to support decision-making concerning reimbursement of cancer rehabilitation programs in the Netherlands.

However, several limitations to the study need to be taken into account. Randomization in the current study design was considered not feasible as IHNR is provided as reimbursed standard care in the NKI, and is currently not provided in the other centers. Moreover, introducing randomization in the NKI with a “no supportive care” group raises ethical concerns. ‘Therefore, this controlled observational study within different HNC centers was considered to be the most feasible design. To best approach the internal validity of a randomized study, we will adjust for case mix by using propensity score analysis [44]. Furthermore, the USC provided by the control group to HNC patients can vary among the different HNC centers. In this study, these centers are merged in one control group. Differentiation between subgroups of comparable USC will only be feasible in case sufficient number of patients is included in each of these subgroups, which will be challenging especially if one of these groups is relatively well represented in accrual numbers. To minimize the risk of selection bias we recruit sequential cohorts in all participating centers.

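### IHNR is given at one hospital and usual care at six others: the 80% power assumes no between-hospital variance, and patient-level adjustment cannot separate the programme from its hospital

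*Protocol article*

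**What the plan says.** **Who is in which arm.** The Study design section of the protocol article states: "The intervention group consists of all eligible consenting patients treated in the NKI, despite participating or not in the program". The Discussion adds that the other centres do not currently provide the programme. Controls come from six hospitals, three academic and three community (Study design; USC – control group). The protocol expects the content and organisation of care to differ between them.

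**Analysis.** HRQoL is to be compared with a mixed-effects growth model with random intercept and slope, "nested within site (clusters of different hospitals", adjusted for case mix by a propensity score (Statistical analysis). The Discussion gives the purpose: "To best approach the internal validity of a randomized study, we will adjust for case mix by using propensity score analysis".

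**Sample size.** The Power calculation section rests on "a comparison between the intervention and control group at end of follow-up", "using a power (β) of 0.8 and a significance level of 0.05", with an "expected effect-size (Cohen’s d) of 0.5". The target is: "We will recruit until we have included 128 patients in total for this analysis (64 are needed per arm". The section names the method: "we used a one sample t-test power calculation". It calls the cross-sectional basis conservative and expects it to absorb design effects, giving attrition and baseline differences as examples. Clustering by hospital is not mentioned.

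**The concern.** The sample size treats 128 patients as independent, while the primary model treats them as clustered in seven hospitals. Treatment is constant within every hospital, so the arm comparison sets one cluster against six. With fixed hospital effects the IHNR effect could not be estimated. With random hospital effects it can, but only by assuming that the NKI's own effect comes from the same distribution as those of the six control hospitals, whose variance must be estimated from those six alone.

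Two things follow. The stated 80% power does not carry over to the planned analysis if hospitals differ. And a difference between arms may reflect anything else that distinguishes the NKI from the other hospitals. A propensity score built on patient characteristics balances case mix but does not address this. The abstract and the Discussion link a positive result to national provision and reimbursement, so the wording of the conclusion matters.

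**Working it through.** **Inputs.** From the protocol: d = 0.5, alpha 0.05 (sidedness not stated), power 0.80, 64 per arm, 1 intervention hospital, 6 control hospitals, comparison at the end of follow-up (T4). Assumed, because the protocol gives no value: the ICC, meaning the share of the variance of the T4 summary score that lies between hospitals within an arm, taken as 0.01 to 0.05.

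**Step 1: reproduce the plan's figure.** A two-sided two-sample t-test on independent patients needs 63.8, so 64 per arm, with power 80.1% (normal approximation 80.7%). The one-sample test that the text names would need 34, and a one-sided two-sample test 51. The 64 is therefore the two-sample, two-sided figure. As it is the exact requirement, any reserve must come from the repeated measures.

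**Step 2: add the 1-versus-6 structure on the same T4 basis.** With total SD 1 and control hospitals of equal size,

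Var(diff) = ICC × (1 + 1/6) + (1 − ICC) × (2/64).

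Power uses z = 0.5/SE − 1.96, with the site variance taken as known. The difference detectable with 80% power is 2.80 × SE.

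| ICC | Var(diff) | SE | Design effect (Var ÷ 0.03125) | Power | Detectable d |
|---|---|---|---|---|---|
| 0 | 0.0313 | 0.177 | 1.00 | 81% | 0.50 |
| 0.01 | 0.0117 + 0.0309 = 0.0426 | 0.206 | 1.36 | 68% | 0.58 |
| 0.02 | 0.0233 + 0.0306 = 0.0540 | 0.232 | 1.73 | 58% | 0.65 |
| 0.05 | 0.0583 + 0.0297 = 0.0880 | 0.297 | 2.82 | 39% | 0.83 |

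The first term does not shrink as patients are added. On this basis 80% power cannot be reached with any number of patients once the ICC exceeds (0.5/2.80)² ÷ (7/6) ≈ 0.027.

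**Step 3: estimate the site variance instead of knowing it.** This used 4,000 simulated T4 data sets per setting, with hospital sizes 64, 11, 11, 11, 11, 10 and 10 and a REML fit with a random site intercept.

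| ICC | Power, Wald z | Type I error, Wald z | Power, t on 5 df |
|---|---|---|---|
| 0 | 62% | – | 42% |
| 0.01 | 58% | 5.6% | 39% |
| 0.02 | 54% | 8.2% | 37% |
| 0.05 | 46% | 11.7% | 32% |

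Two features need explaining. The 62% at ICC 0 is below the 81% of Step 2 because REML sometimes finds a positive site variance by chance, not because hospitals differ. The 46% at ICC 0.05 is above the 39% of Step 2 because the test no longer holds its level. The site variance is estimated as zero in 33% to 59% of runs. The t reference on 7 − 2 = 5 df is very conservative at small ICC: repeat runs gave type I error of about 1%, 1.4% and 3.1% at ICC 0, 0.01 and 0.02, and 5.8% at 0.05.

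**Step 4: what baseline data can recover.** Let r be the assumed within-hospital correlation of T0 with T4. Baseline adjustment that reduces only the patient-level part gives

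Var(diff) = ICC × (7/6) + (1 − r²)(1 − ICC)(2/64).

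Power (site variance known) at r = 0.5 is 76%, 64% and 42% at ICC 0.01, 0.02 and 0.05. At r = 0.6 and ICC 0.01 the variance is 0.0117 + 0.64 × 0.0309 = 0.0315, which gives 80.5%.

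If the target is instead the change from T0 to T4, and hospitals do not differ in change, Var(diff) = 2(1 − r) × (2/64). Power is then about 81% at r = 0.5 and 89% at r = 0.6.

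**The case against.** The strongest reply is that Steps 2 and 3 do not describe the planned model. The protocol plans a growth model over T0 to T4, not a T4 comparison with a random site intercept. In a group-by-time contrast, a stable hospital difference is present at T0 as well as T4 and cancels; only between-hospital variance in change remains. This stands. The T4 figures answer the protocol's own power basis and are not the power of the growth model. It does not dispose of the point: hospital effects that develop during treatment and follow-up do not cancel, and the text does not make clear whether the slope, as well as the intercept, varies by site.

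A reader might infer that 64 per arm definitely fails to give 80% power. The document does not support that. It gives no ICC, and Step 4 shows favourable cases that reach 80%. Nor should anyone read across the type I error that would arise if hospital were ignored (about 9% to 24% at ICC 0.01 to 0.05), because this plan includes site. At ICC 0.01 the Wald test is close to nominal.

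The protocol can also say that it admits non-randomisation and varying usual care, and that it claims propensity adjustment for case mix only. That is fair: it does not claim to remove hospital effects. But it never says that the arm comparison is also a comparison of one hospital with six. Finally, the list of design effects is given as examples, so clustering might be meant to fall under it. No reserve is quantified, however, and the variance term for a single hospital is not one that a cross-sectional basis covers.

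**Conclusion.** The concern holds in a limited form. Two parts follow from the document alone: treatment coincides with hospital, 1 against 6, and the 80% power belongs to a two-sample test on independent patients. The size of the shortfall rests on an assumed ICC and a T4 comparison. At ICC 0.01 to 0.05, power is about 68% to 39% with known site variance, or about 58% to 46% with REML and Wald z, where type I error is roughly 6% to 12%.

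In the planned growth model the loss depends on between-hospital variance in change and on the correlation with baseline. It may be small: 80% is reached, for example, with ICC up to about 0.01 and r of at least about 0.6, using a normal reference. Whatever the ICC, patient-level propensity adjustment cannot separate IHNR from other features of the NKI, and enrolling more patients at the same seven hospitals would not change that.

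**What to change.** 1. **Power statement.** Say that 80% assumes independent patients and no between-hospital variance, in level or in change. Name the two-sample two-sided t-test, and label 0.8 as 1 − β. Give power over a range of ICCs for the planned site-nested model, with the assumed baseline correlation stated.
2. **Primary model.** Keep site in the model for both intercept and slope, and use a small-sample correction such as Kenward-Roger. Treat t on 5 df only as a conservative bound, not as an equivalent, because its type I error falls well below nominal at small ICC. As a sensitivity analysis, leave out each control centre in turn, including the one that offers multidisciplinary care. A separate analysis plan may already contain some of this; its absence from the article is not the complaint.
3. **Conclusion.** Word the result as care at the IHNR hospital versus care at six usual-care hospitals, and state that propensity adjustment does not separate IHNR from other effects of the NKI.

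The cost is wider confidence intervals and a less favourable power statement. No extra patients are needed.

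### The satisfaction comparison is assigned a chi-square test for trend with no case-mix adjustment named, and unmet needs gets description only, although the same section says all analyses are propensity-adjusted

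*Protocol article*

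**What the plan says.** All of the analysis text is in the Statistical analysis section of the protocol article.

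- **General rule**, at the end of the paragraph on HRQoL: "All analyses will be performed on an ‘intention to treat’ basis and will be adjusted for case mix by means of a propensity score analysis".
- **Satisfaction:** "Group differences in evaluation of satisfaction will be tested by means of the Chi-square test for trend".
- **Unmet needs:** "Employment status, unmet needs and satisfaction of the patient will be analysed using descriptive statistics". No between-group test or model is named for unmet needs.
- **Timing:** "The unmet needs and the satisfaction of the patient will be evaluated cross-sectional, at each time point and at T4 respectively".
- **Work status**, for contrast: a generalized mixed-effects model with a logistic link, used to estimate the effect of IHNR at each time point.

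Elsewhere in the article:

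- Under Unmet needs of the patient, the item is binary and is asked from T1 to T4: "It comprises of a yes-no question to ask whether there were needs not addressed during the last 3 months".
- Under Patient satisfaction, the item is scored "using a five-point scale, with 0 indicating very unsatisfied and 5 is very satisfied".
- The Discussion explains that randomisation was not feasible, presents propensity adjustment as the way to come closest to a randomised study's internal validity, and expects IHNR to address unmet needs better.

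**The concern.** The general rule has no exceptions, but the method named for satisfaction does not carry it out. In its ordinary form, a chi-square test for trend takes a two-group by ordered-category table and nothing else. The article names no matched, weighted or stratified version. An analyst who follows the text literally would compare patients from one specialised cancer hospital with patients from six other hospitals with no allowance for differences in case mix.

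This matters because adjustment is the only protection against confounding that the design offers. Any difference in satisfaction could then reflect who is treated where. For unmet needs the gap is different: the authors hold a comparative expectation, but the plan contains no comparative analysis that could support it.

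**Working it through.** **1. Passages side by side.**

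| Outcome | Type and timing | Method named | Propensity step named with it |
|---|---|---|---|
| HRQoL | continuous, T0 to T4 | mixed-effects growth model, nested within site | yes, same paragraph |
| Work status | binary, repeated | logistic mixed model | none, but a model can take the score |
| Satisfaction | ordinal, T4 | chi-square test for trend | none |
| Unmet needs | binary, T1 to T4 | descriptive statistics | none |

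Satisfaction is the only one of these outcomes with a formal group comparison whose named method cannot, as it stands, take the score.

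**2. Size of the effect if the test is run as named.** The documents give no imbalance or correlation figures, so these are assumptions:

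- d = difference between arms in a confounder, 0.2 to 0.5 SD
- r = correlation of that confounder with satisfaction, 0.3 to 0.5
- n = 64 per arm, from the Power calculation section
- no effect of IHNR; nominal two-sided 5% level

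On an underlying continuous scale with unit variance, confounding alone shifts the arms apart by d × r. The test statistic is then centred at λ = d × r × √(n/2), with √(64/2) = 5.657. The rejection probability is Φ(λ − 1.96) + Φ(−λ − 1.96).

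A simulation was also run with 4,000 runs per setting and five or six equally likely categories. It compared a plain trend test with a trend test stratified on quintiles of the confounder score.

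| d | r | λ | Normal approximation | Simulated, plain (5 / 6 categories) | Simulated, stratified (5 / 6 categories) |
|---|---|---|---|---|---|
| 0.2 | 0.3 | 0.339 | 0.0526 + 0.0107 = 0.063 | 0.060 / 0.063 | 0.050 / 0.049 |
| 0.2 | 0.5 | 0.566 | 0.0816 + 0.0058 = 0.087 | 0.082 / 0.085 | 0.051 / 0.055 |
| 0.5 | 0.3 | 0.849 | 0.1332 + 0.0025 = 0.136 | 0.131 / 0.120 | 0.049 / 0.052 |
| 0.5 | 0.5 | 1.414 | 0.2926 + 0.0004 = 0.293 | 0.263 / 0.268 | 0.057 / 0.053 |

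The Monte Carlo standard error is about 0.003 near 5%: √(0.05 × 0.95 / 4000) = 0.0034. With no imbalance (d = 0), the plain test held its level, at 0.048 to 0.054. The inflation therefore comes from the assumed confounding and not from the test itself.

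The stratified result is a favourable case, because the simulated score is the confounder itself. A real propensity score removes only what was measured.

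**3. Scale.** The integers 0, 1, 2, 3, 4, 5 make six codes; a five-point item would run 0 to 4 or 1 to 5. In the worst setting, five and six categories give 0.263 and 0.268, so the number of codes barely affects the test.

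**The case against.** **The plan may already cover this.** A propensity score need not enter as a covariate. A trend test on a matched, weighted or stratified sample would satisfy the general rule, and the choice among these could sit in a full protocol or SAP that is not shown. Alternatively, the general rule stands in the HRQoL paragraph and may have been meant for those models only. Both points are fair. A reader might infer that the plan commits to an unadjusted test, but the article never says so. What remains is that it names a specific method which, in its ordinary form, does not meet a rule worded to cover all analyses. If the rule was meant for HRQoL only, its wording is too wide. On either reading the text needs reconciling.

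**Description of unmet needs is defensible.** None of the three hypotheses in the Background names unmet needs or satisfaction, and the Discussion warns that patients may not recognise some of their needs. This stands: description alone is a legitimate choice, provided that no comparative conclusion is drawn from it.

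**Clustering by hospital.** A reader might go further and charge this test with the error inflation caused by ignoring hospital. Under assumed intraclass correlations of 0.02 to 0.05, simulated type I error was about 13% to 22%. It was nearly the same with and without stratification on the confounder score. It is therefore a consequence of comparing one hospital with six. That limitation applies to the whole design and does not measure what the missing case-mix adjustment does. The documents give no intraclass correlation either.

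**Scale label.** A reader might infer that the miscounted scale distorts the trend test. The comparison of five and six codes above shows that it does not.

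**Conclusion.** The point holds as an inconsistency between a general adjustment rule and the method named for satisfaction, together with an unmet-needs outcome that has a comparative expectation but no comparative analysis. If the satisfaction test is run exactly as named, its type I error is about 6% to 27% at a nominal 5% under the assumed confounding. Stratifying on the confounder score brings it to about 5% to 6%. Those figures rest on assumed imbalance and correlation, on all 64 patients per arm answering at T4, and on a score that captures the confounder. They illustrate the size of the problem and do not estimate what this study will show.

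The consequence is limited to secondary outcomes. The primary HRQoL analysis and the sample size are unaffected. The scale description is a labelling slip.

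**What to change.** 1. **Satisfaction.** Replace the plain trend test with a propensity-adjusted ordinal analysis: either a proportional-odds model with group and propensity score, or a trend test stratified on the propensity score.
2. **Unmet needs.** If IHNR and USC are to be compared, use the logistic mixed model already planned for work status, with the propensity score, over T1 to T4, and report adjusted proportions per visit. Otherwise state that unmet needs is descriptive only and supports no between-group claim.
3. **Site.** Any site term must be random, because a fixed term cannot be separated from group when IHNR is given in one hospital. State as a limitation that no model can separate IHNR from that hospital.
4. **General rule.** Make its scope match the outcome-specific methods.
5. **Scale.** Reconcile the five-point label with the 0 and 5 anchors according to the codes actually printed on the questionnaire, which is not shown.

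The cost is a few sentences of analysis text. The data and methods are already in the plan, and recruitment does not change.
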